**Methods:**

This mixed-methods controlled pilot trial will test the feasibility of the proposed supervision model in making quality-assured surgery available at DLHs. Firstly, the study will conduct a quantitative assessment of surgical service delivery at district facilities, looking at hospital preparedness, capacity and productivity, and how these are affected by the intervention. Secondly, the study will monitor changes in referral patterns from DLHs to a higher level of care as a result of the intervention. Data on utilisation of the mobile based-support network will also be collected. The analysis will compare changes over time and between intervention and control hospitals. The third element of the study will involve a qualitative assessment to obtain a better understanding of the functionality of DLH surgical systems and how these have been influenced by the intervention. It will also provide further information on feasibility, impact and sustainability of the supervision model.

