## Research objectives

The specific objectives of this research study are as follows:To determine whether the intervention is able to affect change in surgical activity at district level. We will assess whether supervision and mentoring will enhance the capacity of district surgical teams, leading to changes in surgical activity. In particular, we expect to observe (1) an increase in the number of procedures regularly performed by the participating hospitals compared to surgical activity before the intervention, as more district clinicians will be trained in handling general surgical procedures and (2) a change in the range of surgical cases done in DLHs as new procedures will be introduced and performed by local teams, where the SOT deems this to be appropriate to local needs, staff skills and resourcesTo establish the feasibility of the intervention to improving skills of local surgical teams (including surgery, anaesthesia and nursing staff) as individuals and as a group. We will test whether the support offered through supervision and mentoring will change confidence (as a proxy measure of skills) and preparedness of local teams in performing essential surgical proceduresTo monitor whether the intervention can change referral practices, particularly whether it can reduce the number of unnecessary surgical cases referred by district hospitals compared to the number before the intervention because skills and confidence of DLHs clinicians are expected to improveTo determine the feasibility and acceptability of the remote consultation mechanism established by the intervention and to assess any changes in communication between DLHs and RHs and in clinical decision-making. The project’s mobile phone-based communication network will give DLH clinicians access to specialist opinion at RHs and will allow real-time consultations with RHs clinicians. The communication network will also facilitate timely feedback to district teams on referred cases

In parallel, the research will investigate process-related aspects of the intervention to determine feasibility and replicability of the proposed regular supervision model, particularly in light of the shortage of specialists at referral institutions and limited budgets. It will identify obstacles and enablers to DLHs supervision done by specialists located at RHs, to build an understanding of what processes need to be put in place for the supervision to be successful in achieving the above objectives.

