### Research sites

The intervention will be delivered in 30 district-level hospitals (DLHs) in three African countries—Malawi, Zambia and Tanzania—for 24 months. The evaluation will include 4 months of baseline data and 24 months of intervention data. Malawi, Zambia and Tanzania were chosen because of their political stability, long-term presence of the consortium members on the ground and logistical considerations related to feasibility of implementation. Malawi and Zambia were the settings of the previous COST-Africa project, whose findings led to the SURG-Africa intervention. In each country, a large catchment population was purposively selected in consultation with local ministries of health, the geographical focus is country-wide in Malawi; adjoining districts in Southern, Central, Western and Lusaka provinces in Zambia and the Northern Zone in Tanzania. Study sites (selected districts) will be determined by the location of referral institutions and respective DLHs that fall within the referral network of that referral hospital. A randomised design for the allocation of hospitals to the intervention and the control arms is not possible because of the small sample sizes (availability of suitable DLHs within these referral networks) and the nature of the intervention (described below). Control hospitals will therefore be located outside these areas and will refer patients to different referral hospitals. However, the risk of selection bias is low because DLHs are fairly homogeneous within each study country regardless of their location, thus reducing the chance of imbalance in characteristics in the distribution of treatment versus control groups [50–52]. Hospitals that do not meet the inclusion criteria (below) or that are already demonstrating significantly better surgical performance than would be expected at a DLH will be excluded from the sample. The precise selection of control hospitals will be determined by the results of the situation analysis conducted prior to the kick off of the intervention. The situation analysis will constitute the baseline for our study (month 0). It will collect information about the surgical capacity of district hospitals using theatre records (volume and range of surgery), Personnel, Infrastructure, Procedures and Supplies (PIPES) scores and additional questions about referral patterns, information management systems, quality control practices and availability of staff (NPCs) not covered by the PIPES questionnaire. This information will be analysed aiming to determine hospital suitability to be part of the intervention based on the following criteria.

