#### Objective 1: Surgical preparedness, capacity and productivity

The first objective of our study is to undertake a quantitative assessment of surgical service delivery at district hospitals and how this is affected by the intervention, considering three dimensions: hospital preparedness, capacity and productivity. Each dimension will be measured using quantitative indicators reflecting our overall research aims and conceptual framework, as described in the previous sections. Table 2 provides an overview of objective 1 including indicators, data sources, instruments and planned analyses.

**Table 2 Tab2:** Overview of objective 1

	Indicators	Data collection instruments	Measurement
Preparedness - change in surgical capacity of DLH facilities	Change in Personnel Infrastructure Procedures Equipment Supplies (PIPES) index scores	PIPES questionnaire	Measured at baseline with periodic follow-ups (month 0, month 12, month 24 of the intervention)
Capacity - change in skills of DLH staff	Number of intervention DLH staff who are reported as competent in doing index procedures Intervention DLH staff self-reported surgical skills confidence levels	PIPES questionnaire Self-reported surgical confidence tool	Before-and-after controlled comparison
Productivity - increase in surgical outputs and outcomes	Change in number of index surgical procedures performed by DLHs Types and numbers of new procedures introduced into DLHs Change in surgical mortality rates	PIPES questionnaire Monthly data collection from DLHs operating theatre registers	Comparing differences: (1) before and after and (2) between intervention and control hospitals

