It is expected that the intervention will change the *surgical productivity* of DLHs in terms of number of common surgical procedures performed and types and numbers of new procedures introduced, which form the primary endpoint of the study. Monthly numbers of Caesarean sections are typically used to assess the volume of major surgery at DLHs. SURG-Africa will monitor this parameter and include a larger set of core general surgical procedures done in DLHs, identified through the initial situation analysis. This will allow us to develop an index of key procedures to compare differences in numbers and types of procedures: (1) before and after and (2) between intervention and control hospitals, at both group and individual hospital level of analysis. In parallel, the evaluation will track intra-hospital mortality rates to monitor possible changes in surgical outcomes as surgical activity is expected to increase.

Our study will also analyse whether the intervention will result in changes in the key drivers of DLH productivity, namely the *capacity* of local surgical teams and overall *preparedness* of the facilities to perform surgery. The change in staff capacity will be measured through a before-and-after controlled comparison of the number of intervention DLH staff who is reported as competent in doing index procedures. Another measure is self-reported surgical confidence as a proxy parameter for surgical skills. This tool has been tested and validated by previous studies, showing positive correlation between confidence of surgical providers and assessment of skills by their supervisors [57].

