### Data analysis

The analysis plan comprises comparison of the changes from baseline to end of study (after 24 months of the intervention) in primary and secondary endpoints. The analysis will involve descriptive and summary statistics (frequency counts) for the quantitative data and comparisons of means (with the relevant parametric or non-parametric test), where before-and-after changes are expected. Results will be presented with 95% confidence intervals. Significance will be set at 5%, two-tailed. We intend to have multiple time-points at which data will be collected. Repeated measures will be made to analyse trends in the primary and secondary outcomes, making the assumption that any secular trends (government investments, staff deployments, etc.) will occur irrespective of the allocation of hospitals to either intervention or control arms of the trial. However, even if this is not the case, important secular activities and events will be captured through the qualitative study phase. This is particularly important in LMICs where attention to surgery is growing and other externally-driven activities may take place [6]. The qualitative data will be analysed using the ‘top-down’ method of theme identification [62].

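### The protocol lists before-after and between-arm comparisons for the primary endpoint but does not fix the intervention effect as the between-arm difference in hospital-level change

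*Protocol article*

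**What the plan says.** The protocol article describes the comparison in several places, and they do not settle on one quantity.

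- **Research objectives.** The first expected result is "an increase in the number of procedures regularly performed by the participating hospitals compared to surgical activity before the intervention". The reference is the hospitals' own past.
- **Objective 1, Table 2, Productivity row.** The measurement is "Comparing differences: (1) before and after and (2) between intervention and control hospitals". The text below the table repeats the two comparisons for the primary endpoint, "at both group and individual hospital level of analysis".
- **Data analysis.** The section opens: "The analysis plan comprises comparison of the changes from baseline to end of study (after 24 months of the intervention) in primary and secondary endpoints". That sentence does not name the arms. The tests are then described as "comparisons of means (with the relevant parametric or non-parametric test), where before-and-after changes are expected", with "Significance will be set at 5%, two-tailed".
- **Abstract, Methods.** "The analysis will compare changes over time and between intervention and control hospitals".

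The Data analysis section also assumes that secular trends do not depend on arm. If they do, it relies on the qualitative phase to record the relevant events. The Control hospitals section says that both groups are followed prospectively and compared.

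**The concern.** Neither listed comparison estimates the intervention effect by itself. Before-after change within the intervention arm contains whatever would have happened anyway, and the article says that attention to surgery is growing in these settings. The between-arm comparison contains any starting difference between regions that were chosen purposively.

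Only the between-arm difference in change removes a trend common to both arms and a stable baseline difference together. If it is not named in advance, a significant before-after rise would match the first objective as worded and could be reported as the effect, even with the same rise in the controls. The study is meant to inform national scale-up, so the choice of contrast has consequences.

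**Working it through.** The article gives no power, effect size, SD or calculated sample size, so there is no planned figure to reproduce. The check asks how each candidate comparison behaves when the intervention does nothing.

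**Inputs from the article**
- 30 intervention hospitals, 4 baseline months and 24 intervention months (Research sites).
- Two-sided 5% level (Data analysis).
- Eligible hospitals: 22 + 27 + 36 = 85 (Sample size). If the 30 intervention hospitals come from these, at most 85 − 30 = 55 controls remain. The number of controls is not stated.

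**Assumed, not in the article**
- Secular rise common to both arms: 0 to 20%.
- SD of hospital log-change, s: 0.2 to 0.4.
- Between-hospital log-SD: 0.5.
- Mean of 40 procedures per month, Poisson counts.
- 30 or 55 controls.

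**Step 1. Before-after test in the intervention arm.** For a paired t-test on 30 hospital log-changes, the noncentrality is ln(1 + rise) / (s / √30), with critical value t(0.975, 29) = 2.045. For a 10% rise, ln(1.10) = 0.0953:
- s = 0.2: 0.0953 / 0.0365 = 2.61
- s = 0.3: 0.0953 / 0.0548 = 1.74
- s = 0.4: 0.0953 / 0.0730 = 1.31

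Probability of a significant result with no intervention effect:

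| Common rise | s = 0.2 | s = 0.3 | s = 0.4 |
|---|---|---|---|
| 5% | 25% | 14% | 10% |
| 10% | 71% | 39% | 24% |
| 20% | 99.8% | 90% | 68% |

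A simulation of 2,000 trials per setting, with Poisson monthly counts, gave 66% (s = 0.2) and 37% to 40% (s = 0.3) at a 10% rise. It agrees with the formula apart from the added count noise.

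**Step 2. Between-arm comparison in the follow-up period, hospital as unit.** A common rise cancels, and simulated rejection was 4% to 6% at every rise from 0 to 20%. A starting difference does not cancel. Ignoring count noise, with s = 0.3 and 30 controls, the standard error of the difference in log means is √[(0.5² + 0.3²) × 2/30] = √0.0227 = 0.151. A baseline imbalance of 0.3 on the log scale (a ratio of e^0.3 = 1.35) gives 0.3 / 0.151 = 1.99, or about 50% rejection; the simulation gave 49%. The same formula gives about 26% for an imbalance of 0.2 and 10% for 0.1.

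**Step 3. Difference between arms in hospital log-change.** A Welch t-test on the hospital changes rejected in 4.4% to 5.8% of simulated trials across rises of 0, 10 and 20%, s = 0.2 and 0.3, and 30 or 55 controls. With the 0.3 imbalance and a 10% rise it rejected in 4.6%.

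**The case against.** The strongest reply is that the article already implies the right contrast. Its Data analysis section speaks of comparing changes, the abstract speaks of change over time and between arms, and the Control hospitals section has both groups followed and compared. An assumption that secular trends are the same in both arms has a purpose only if changes are compared between arms. This stands as far as it goes: difference-in-differences is compatible with the text. It is not fixed by the text, because Table 2 and the objective point to other contrasts and nothing ranks them.

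Second, this is an exploratory feasibility pilot, and no rule makes a significant before-after test the criterion for success or scale-up. The objective states an expectation, not a test. That lowers the stakes but does not settle which result counts as the effect.

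Third, the sizes rest on assumed values. The article argues for a low risk of imbalance on the ground that "the risk of selection bias is low because DLHs are fairly homogeneous within each study country regardless of their location", and it plans controls with similar productivity, PIPES scores and staffing. Real imbalance may therefore be below 0.3, which is why smaller values are shown.

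A reader might infer more than the text supports:
- **That hospital-months are pooled as independent observations.** No sentence says so, and the hospital is named as a level of analysis. How repeated months and clustering are handled may be left to an analysis plan not shown.
- **That each hospital is tested at 5%.** The article describes a level of comparison, not a set of hypothesis tests, and expects that a trend may not appear in every facility.
- **That a common secular rise biases both comparisons.** It inflates only the before-after one.
- **That one particular regression model is required.** A simple hospital-level comparison of changes already holds the error rate.

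**Conclusion.** The concern holds as a failure to fix the primary contrast. The article lists a before-after and a between-arm comparison for the primary endpoint without stating that the intervention effect is the between-arm difference in hospital-level change. It does not rule that reading out.

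The consequence depends on which comparison is reported as the effect. With no true effect and an assumed common 10% rise, relying on before-after gives a false positive in roughly 24% to 71% of trials. Relying on the post-period arm comparison keeps about 5% if the arms start level, but gives about 49% under an assumed 0.3 log imbalance. The difference in changes gives about 4% to 6%. The ordering is stable over the range examined; the exact percentages are not, since none of the variance or trend values come from the article.

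The difference in changes is valid only if trends are parallel. Qualitative records of events can help explain a departure from that, but they cannot correct the estimate.

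**What to change.** State one primary contrast in the Data analysis section and align Research objectives, Table 2 and the Objective 1 text with it:

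- The intervention effect is the arm-by-period difference in hospital-level index-procedure counts, with the hospital as the cluster and country as stratum. Either a comparison of hospital-level changes or a mixed model for counts would serve. Report it with a 95% confidence interval.
- Apply the same contrast to the number of new procedures introduced, since these are also part of the primary endpoint.
- Label within-arm before-after results and single-hospital results descriptive.
- Say that parallel trends is an assumption of the estimate which the qualitative data cannot correct.

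The procedure counts are already planned in both arms, so the change is to wording and analysis, and it should be made before outcome data are seen. The cost is slightly more analysis work and a wider interval than before-after alone. With equal SD of change in both arms, the standard error grows by √(1 + 30/controls): √2 = 1.41 with 30 controls, and √(1 + 30/55) = 1.24 with 55.

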
Inclusion criteria:Capacity to deliver Bellwether surgery: caesarean sections, laparotomy and treatment of open fracture [53]Accessibility by carLocation within the designated referral network in each country, with Livingstone Central Hospital or University Teaching Hospital in Zambia, Queen Elizabeth Central Hospital in Malawi, and Kilimanjaro Christian Medical Centre in Tanzania as focal points for referrals

Exclusion criteria:No surgical capacity to deliver Bellwether surgeryNo accessibility by carRelatively high surgical capacity (to be determined by an average Personnel, Infrastructure, Procedures, Equipment and Supplies (PIPES) index score—see Table 2 [54])Having any specialists (i.e. trained surgeons or anaesthesiologists)

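### Three or four referral networks stand behind the 30 intervention hospitals, so hospital-level 95% intervals and 5% tests are too narrow if changes correlate within networks beyond country-wide trends

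*Protocol article*

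**What the plan says.** Delivery and allocation follow the referral network:

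- Research sites gives the size of the intervention arm: "The intervention will be delivered in 30 district-level hospitals (DLHs) in three African countries".
- The same section says how sites are chosen: "Study sites (selected districts) will be determined by the location of referral institutions and respective DLHs that fall within the referral network". Allocation is not randomised, and controls lie outside these areas and refer to other hospitals.
- The inclusion criteria name four referral hospitals (two in Zambia, one in Malawi, one in Tanzania), the list ending "Kilimanjaro Christian Medical Centre in Tanzania as focal points for referrals".
- The section The intervention says that supervisors come from the main referral hospital of each area. Objective 2 makes the group of district hospitals around one central hospital the unit through which supervision is delivered and evaluated.
- Table 1 draws controls from two regions in Malawi, four provinces in Zambia and three regions in Tanzania. The section Control hospitals says that they receive no supervision from the project's teams.

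On analysis, Objective 1 compares numbers and types of procedures before and after and between arms, "at both group and individual hospital level of analysis". Data analysis plans "comparisons of means (with the relevant parametric or non-parametric test), where before-and-after changes are expected", then sets the interval and significance level: "Results will be presented with 95% confidence intervals. Significance will be set at 5%, two-tailed". It also mentions repeated measures for trends, and assumes that secular trends are unrelated to arm. Departures from that assumption are left to the qualitative study.

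**The concern.** Hospitals in one intervention network share a supervising referral hospital, the specialists who answer their calls, and a regional setting. If supervisors there become scarce, or a regional authority moves staff or money, several hospitals change together. Analysing change from baseline removes constant differences between networks, but not these network-specific movements over time. Because arm coincides with network or region, such movements add to the between-arm difference, and the spread between individual hospitals does not fully reflect them.

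A standard two-sample interval would then be too narrow, and the 5% test would reject too often when supervision has no effect. The Discussion intends the results to guide national scale-up, where other teams would supervise. An interval that leaves out variation between networks says little about those teams.

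**Working it through.** **Inputs from the document.** 30 intervention hospitals in three countries; four named referral hospitals, or three networks if only one serves the Zambian intervention area, which Table 1 limits to one province; 2 + 4 + 3 = 9 control regions or provinces; 5% two-sided (z = 1.96).

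**Assumptions.** The document gives no ICC, standard deviation, power or number of control hospitals. I take 10 hospitals per country per arm, and split the controls 5+5 (Malawi), 3+3+2+2 (Zambia) and 4+3+3 (Tanzania). ICC means the correlation of change scores within a network or region, and is varied from 0.01 to 0.20.

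**Plan's own figure.** There is no sample size calculation to reproduce. The nominal level, 2 × (1 − Φ(1.96)) = 0.05, holds at ICC 0.

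**Step 1, intervention arm.** Three networks of 30/3 = 10: design effect = 1 + 9 × ICC.

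**Step 2, control arm.** The squared region sizes sum to (25+25) + (9+9+4+4) + (16+9+9) = 110. The design effect is 1 + (110/30 − 1) × ICC = 1 + 2.67 × ICC.

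**Step 3, difference between equal arms.** DE is the average of the two. The interval should be √DE times as wide, and the actual type I error is 2 × (1 − Φ(1.96/√DE)).

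| ICC | DE, intervention | DE, control | DE, average | Width factor | Type I error, formula | Type I error, simulated t test |
|---|---|---|---|---|---|---|
| 0.01 | 1.09 | 1.03 | 1.06 | 1.03 | 0.057 | about 0.06 |
| 0.05 | 1.45 | 1.13 | 1.29 | 1.14 | 0.085 | about 0.09 |
| 0.10 | 1.90 | 1.27 | 1.58 | 1.26 | 0.119 | about 0.12 |
| 0.20 | 2.80 | 1.53 | 2.17 | 1.47 | 0.183 | about 0.19 |

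**Step 4, four intervention networks.** With 30/4 = 7.5 hospitals each, the intervention design effect at ICC 0.10 is 1 + 6.5 × 0.10 = 1.65. The average is (1.65 + 1.27)/2 = 1.46, and the type I error is 2 × (1 − Φ(1.96/1.21)), about 0.10.

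**Step 5, other control layouts.** If all controls were independent, simulation gives 0.057, 0.080, 0.104 and 0.157 at the four ICCs. If controls also formed three networks of 10, the formula gives 0.061, 0.104, 0.155 and 0.242, but Table 1 does not describe that layout.

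**Step 6, correlation that is country-wide.** Both arms lie in the same three countries, so a country-wide movement cancels when the arms are balanced by country. With half of the correlated variance country-wide, simulation (40,000 runs, nine control regions) gives 0.065, 0.080 and 0.116 at total ICC 0.05, 0.10 and 0.20. With all of it country-wide, it gives 0.048, 0.041 and 0.035, slightly conservative.

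**Step 7, what the networks can support.** A t test on network means holds its level (simulated 0.048 to 0.052 with three networks per arm). However, it has 4 degrees of freedom with three networks per arm (critical value 2.78) or 6 with four (2.45), against 2.00 at 58 degrees of freedom for 60 hospitals.

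**The case against.** The strongest objection is that the point rests on silence. The article does not say that hospitals are treated as independent; it promises whichever test is relevant, and repeated measures. Random effects and degrees of freedom are commonly left to a full protocol or analysis plan, and neither is shown. This stands as far as it goes: independence is an inference, and no missing model detail is criticised here. But the article itself fixes allocation by network, a comparison of means, the confidence level and the error rate. Followed as written, these overstate precision under any network-specific correlation.

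A reader might also infer that all hospitals in an arm share one team and one region. The documents do not support that. Controls have no team and come from nine regions or provinces, the intervention arm covers three countries, the Tanzanian intervention area alone covers two regions, and the number of teams per referral hospital is not stated. Nor can the between-arm result be read as a contrast of a strong team with an average one, since only one arm has teams.

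Third, a network random effect would be hard to estimate from three or four networks, and would pair supervising networks in one arm with administrative regions in the other. This is right, and the remedy should not depend on such a term. Finally, for country-specific models in an exploratory pilot, inference limited to the teams studied is legitimate, provided that it is labelled so.

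**Conclusion.** The point holds conditionally. With arm set by referral network or region and three or four networks behind the intervention arm, hospital-level intervals and tests are too narrow if changes correlate within networks beyond country-wide trends. Under the stated layout, the harm runs from slight at ICC 0.01 (about 0.06 instead of 0.05) to serious at ICC 0.20 (about 0.19, with an interval that should be nearly half as wide again). Four networks instead of three, or a country-wide share of the correlation, reduces it.

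It would go too far to say that the 5% level and 95% coverage certainly fail: the documents give no ICC, and if all the correlation is country-wide there is no inflation. Severity is moderate. The study describes itself as an exploratory pilot, but its results are meant to inform national scale-up, and the present wording does not limit the inference to the teams studied.

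**What to change.** Change the Data analysis section in three ways:

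1. Estimate the between-arm difference in change within each country, and show these country or network estimates beside the pooled one.
2. Add a sensitivity interval for the pooled difference that allows for network and region correlation over a stated range, for example ICC 0.05, 0.10 and 0.20. Under the layout assumed above this multiplies the width by 1.14, 1.26 and 1.47; recompute the factors from the actual numbers of hospitals per network and region.
3. State that the unwidened interval and the 5% test apply only to the networks and teams studied, and do not by themselves support a claim about other teams at national scale-up.

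A network random effect with small-sample degrees of freedom is optional, since three or four networks may not support it. The cost is a change of wording and a wider, less favourable interval. No new data are needed.
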